### Study Participants

We will identify potential participants by reviewing inpatient census and clinic schedules within Epic and contacting them by phone and email. Participants' recruitment eligibility includes (1) confirmed cancer diagnosis at an advanced stage, not limited by cancer site, (2) being able to read and understand English, (3) being age ≥60 years, and (4) being willing to provide consent. Participants with dementia, altered mental status, or psychiatric conditions that would prohibit the understanding of informed consent or participation in a simulated encounter are not eligible to enroll in the study. With a study team member, participants will review and complete informed consent in person or by phone before enrollment and review it again upon arrival for the simulations.

### Ethical Considerations

This study was reviewed and approved by the University of North Carolina at Chapel Hill (approval number 24-1566). Participant consent will be obtained electronically through REDCap (Research Electronic Data Capture; Vanderbilt University). Participants will receive US $100 for their participation. Survey data will be recorded in REDCap, a secure web application. Survey data, as well as recordings from mock consultations and interviews, will be deidentified and stored on a secure HIPAA (Health Insurance Portability and Accountability Act)-compliant location managed by the University of North Carolina School of Medicine. Protections will be taken to ensure that confidentiality is maintained, ensuring that all personnel are trained on HIPAA regulations, and restricting data access to study personnel.

### Simulation Preparation

To conduct the simulated encounters, we (1) developed disease briefs, (2) trained medical students, (3) developed 2 simulation scripts, and (4) used a modified situational awareness rating scale to estimate the quality of values-clarification processes.

#### Disease Briefs

Textbox 1 describes 2 disease briefs developed and reviewed by 3 clinical oncologists. Disease briefs included a mock cancer diagnosis and treatment options (delivery, side effects, and efficacy).

Disease briefs for simulated patient-clinician encounters.
**Disease brief 1**

*Cancer diagnosis: “Leukocythemia”—aggressive blood cancer*
**Treatment option 1 (standard option):** Combination chemotherapyDelivery: Infusions 7 days in a row at the infusion center every month plus a chemo pillSide effects: Fatigue, risk of hospitalization, weakness; 95% of patients are admitted for complication of treatment at some point in timeEfficacy: Median survival of 12 months**Treatment option 2 (medically inferior option):** Oral chemotherapyDelivery: Oral pill taken every daySide effects: NoneEfficacy: Median survival of 8 months
**Disease brief 2**

*Cancer diagnosis: “Encephaloid tumor”—lung cancer*
**Treatment option 1 (standard option):** IV chemotherapyDelivery: IV chemo weeklySide effects: Low blood counts, infection risk, weakness (100% of patients)Efficacy: Median survival of 4-5 years**Treatment option 2 (medically inferior option):** Oral chemotherapyDelivery: Oral chemo every daySide effects: Constipation (50%), muscle pain (50%), joint pain (50%), weakness (100%)Efficacy: Median survival of 4-5 years

#### Medical Student Training

Five students from the University of North Carolina School of Medicine were recruited and trained to portray oncologists in the simulated patient-clinician encounters. A member of the research team served as a standardized patient during training. The training process included 2 hours of simulation script review with our research team, 1 hour of observation of an oncologist conducting both VB and NVB simulated encounters, and 6 hours of in-person practice, during which students practiced both types of simulations. To ensure consistency throughout the study, students will be debriefed after each simulated encounter to reinforce standardized engagement with participants.

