**Figure 1 figure1:**
[figure not shown]
Randomized pilot testing study schema. (A) Participants will complete informed consent in REDCap (Research Electronic Data Capture) and participant characteristics in Qualtrics remotely before scheduling to engage in simulations. (B) To ensure balanced participation across the 4 potential pathways, a systematic alternating method in Qualtrics will be used to assign participants to the intervention (VOICE) or control (ACS) groups. (C) After participants complete and review VOICE or the ACS guide, they are prompted to contact the research team to schedule the patient-clinician simulated encounters. Patients are reminded they are preparing for a simulated patient-clinician encounter in which they will be asked to discuss and make a decision regarding a “mock” secondary cancer diagnosis. (D) The order of encounter type (VB vs NVB) will be random using a random number generator in Microsoft Excel. (E) All participants will engage in two (20- to 30-minute) simulated encounters (VB and NVB) in random order, both occurring on the same day. Clinicians (ie, medical students portraying oncologists) will only be blinded as to whether the participants received VOICE or the ACS guide prior to the interaction. Clinicians will be informed of the encounter type to ensure they follow appropriate scripts. Simulated encounters will be held at a single site in the Simulation, Experiential Learning, and Training (SET) Center located at the University of North Carolina at Chapel Hill School of Medicine. Simulated patient-clinician encounters will be audio-video recorded. (F) Participants will complete surveys (CollaboRATE and PrepDM [Preparation for Decision-Making]) and engage in semistructured interviews immediately following each simulation. Our research team will complete observed ratings of encounters (VECTORS and OPTION-5) after simulations have concluded by reviewing the audio-recorded simulations. ACS: American Cancer Society; VECTORS: Values Elicitation and Clarification of Treatment Options Rating Scale; VOICE: Values and Outcomes to Improve Cancer Experiences.

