#### Sample Size and Power

This pilot study was not powered, as its primary objective was to gather preliminary data necessary to inform the design and power calculations of a future, larger-scale study. We aimed to estimate the quality of values-clarification processes during simulated encounters (as measured by VECTORS, ranging from 0 to 100) for intervention and control groups in 2 different simulated encounters (VB and NVB). We will attempt to enroll 11 participants in each pathway to gather preliminary data, for a total of 44 participants.

The preliminary data gathered from this pilot study, as well as other study outcome measures, will inform future work using VECTORS in real-world and simulated encounters.

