#### Primary Outcome—Quantitative

Simulated encounters will be quantified using VECTORS to assess the estimated quality of values-clarification processes that occur between intervention and control groups during both VB and NVB encounters. Interrater reliability for VECTORS will be assessed by calculating the Cohen κ weighted coefficient and discrepancies in ratings. Kappa statistics between 0.61 and 0.80 indicate substantial agreement between raters, and 0.81 to 1.00 indicate almost perfect agreement between raters [48]. Analyses of the 3 domains in VECTORS include the raw scores (rapport building: 0-10; clinician engagement: 0-30; patient engagement: 0-30). Analyses of VECTORS overall scores involve taking the sum of all 3 domains, producing a raw score of 0-70, then rescaling to a score of 0-100.

Descriptive statistics will be used to report the mean and SD for VECTORS overall and by each domain. Mean and SD will be reported as cross-tabulations for all encounters, and by intervention and control for VB and NVB encounters, and for whether clinicians transitioned from NVB to VB encounters due to patient agency (ie, patients initiated a discussion pertaining to their values).

Linear regression models using generalized estimating equation methods will be fit using all patient data from both encounter types (VB vs NVB) to account for repeated measures per patient. These models will objectively estimate differences by group and by encounter type and test for potential interactions to show if the intervention works better in one scenario compared to the other.

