By simulating patient-clinician encounters, we control for potential confounding variables, including clinicians’ values-clarification and SDM behaviors, and randomization of information (VOICE vs ACS guide). As current SDM measures alone may not provide evidence on whether patients are actively engaged in SDM [52], simulations of patient-clinician encounters provide the opportunity to evaluate deviations from a “high-quality” SDM encounter.

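### Five students generate much of the primary score, but the stated model has no student term although the Discussion says clinician behaviour is controlled

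*Protocol article*

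**What the plan says.** - **Who plays the clinician:** "Five students from the University of North Carolina School of Medicine were recruited and trained to portray oncologists in the simulated patient-clinician encounters" (under Medical Student Training). All had the same script review, observation and practice, and each encounter is followed by a debrief.
- **Size and purpose** (Sample Size and Power): "We will attempt to enroll 11 participants in each pathway to gather preliminary data, for a total of 44 participants", and "This pilot study was not powered, as its primary objective was to gather preliminary data necessary to inform the design and power calculations".
- **Encounters** (Figure 1 legend): "All participants will engage in two (20- to 30-minute) simulated encounters (VB and NVB) in random order, both occurring on the same day".
- **Allocation** (Figure 1 legend): for arm, "a systematic alternating method in Qualtrics will be used to assign participants to the intervention (VOICE) or control (ACS) groups"; for order, "The order of encounter type (VB vs NVB) will be random using a random number generator in Microsoft Excel". Students are blinded to arm but know the encounter type. No sentence says how students are assigned to participants, or whether one student plays both of a participant's encounters.
- **Model** (Primary Outcome—Quantitative): linear GEE on both encounters "to account for repeated measures per patient", with group, encounter type and a test of their interaction. The Secondary Outcome section carries the same model over to OPTION-5.
- **Claim** (Strengths and Limitations): "By simulating patient-clinician encounters, we control for potential confounding variables". The sentence goes on to list the clinicians' values-clarification and shared decision-making behaviours among these variables.

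**The concern.** The student is not a neutral background condition here. Three of the seven VECTORS items score the clinician, one scores rapport jointly, and every OPTION-5 item scores clinician behaviour. Primary research question 2 has clinician engagement as its outcome. The nonvalues-based script also leaves judgement to the student, who decides whether a remark is a patient cue and how far to move into the values-based levels.

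Scripts, training and debriefing narrow the differences between students, but they neither measure nor adjust for what remains. The control claim therefore goes further than the stated analysis. Two things are at stake: the precision of the arm and encounter-type contrasts, and the absence of any between-clinician variance from a pilot whose stated purpose is to inform the design and power of a larger study.

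**Working it through.** **Inputs from the article.** 4 pathways × 11 = 44 participants, which reproduces the stated total. 44 × 2 = 88 encounters; 88/5 = 17.6 per student. Clinician items are 30/70 = 43% of the raw VECTORS score; with the joint rapport item, 40/70 = 57%.

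**Assumptions (not in the article).** Total variance 1; patient share 0.30; student share of variance *s* from 0 to 0.30; 22 participants per arm.

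**1. Chance imbalance under random rostering.** With one student per participant, the student part of the arm difference has

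SD = √(5 × 2 × 0.2 × 0.8/22 × *s*) = √(0.0727 × *s*).

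This gives 0.060, 0.085, 0.121 and 0.148 outcome SD at *s* = 0.05, 0.10, 0.20 and 0.30. If students are drawn separately for each encounter, divide by √2: 0.043 to 0.104.

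**2. Is this already inside the standard error?** Yes. At *s* = 0.20 with the same student for both encounters, the remaining variance of the arm difference is 2 × (0.30 + 0.50/2)/22 = 0.0500. The student part is 0.0727 × 0.20 = 0.0145, and √0.0645 = 0.254 in total. A null simulation (6,000 runs per setting) that ignored student rejected in 4.6–5.4% of runs for arm and 4.8–5.3% for encounter type, against a nominal 5%.

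**3. When is it not?** In the same simulation with uneven rosters, at *s* = 0.05 / 0.10 / 0.20:
- students skewed 80/20 by encounter type: false-positive rate for VB/NVB about 10% / 16% / 24%;
- students skewed 70/30 by arm: false-positive rate for arm about 6% / 8% / 10%.

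These rosters are illustrations; the article describes no roster.

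**4. What does a student factor do?** Two encounters per participant, random rostering, 4,000 runs per setting, standard error without → with a five-level student factor:

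| *s* | Arm, same student twice | Arm, two different students | VB/NVB, two different students |
|---|---|---|---|
| 0 | 0.240 → 0.253 | 0.244 → 0.248 | 0.179 → 0.186 |
| 0.05 | 0.241 → 0.248 | 0.245 → 0.244 | 0.178 → 0.176 |
| 0.10 | 0.252 → 0.250 | 0.238 → 0.234 | 0.179 → 0.173 |
| 0.20 | 0.253 → 0.235 | 0.241 → 0.229 | 0.179 → 0.156 |
| 0.30 | 0.260 → 0.224 | 0.234 → 0.218 | 0.178 → 0.141 |

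The cost at *s* = 0 agrees with the closed form √(43/39) = 1.05, within simulation error. The gain for arm is about 5–7% at *s* = 0.20 and 7–14% at 0.30. For VB/NVB with different students it is about 13% and 20%. If one student plays both encounters, that student's general level cancels from VB/NVB and the factor changes nothing there.

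**The case against.** The article is silent on rostering, and silence is not a defect. A roster balanced over the four pathways would fit every sentence, and rostering and covariate lists are often left to the full protocol or analysis plan. Students are blinded to arm, so no route to arm-related skew is stated. Standardisation is substantial: common training, a debrief after each encounter, three mandatory levels in one script, and no unprompted advance in the other. Read in context, control may simply mean control by script. At a small student share, adjustment gains nothing or loses a little, and the study is an unpowered pilot.

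Most of this stands, and it limits the point. A reader might infer that student differences bias the arm comparison, or that a chance imbalance would pass for a tool effect. The documents do not support that: under random rostering the imbalance is part of the ordinary standard error and error rates hold (steps 1 and 2). A reader might also apply the design effect 1 + (17.6 − 1) × *s*, which is 2.66 at *s* = 0.10. That applies to an overall mean, not to contrasts in which students are crossed with arm or encounter type.

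What the objection does not remove is the mismatch on the page. The article states the model's terms and its one source of correlation, and separately claims that clinician behaviour is controlled. Standardisation is described; measurement of, or adjustment for, the student is not.

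**Conclusion.** The point holds as one of precision, reporting and wording. The five students produce 43–57% of the available VECTORS points and all the behaviour that OPTION-5 rates, while the stated model leaves them out and the Discussion claims control. Bias in the arm contrast is not shown.

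Under random rostering, adjustment changes the standard error of the arm difference by between about +5% (students do not differ) and −14% (30% of variance, same student twice). For VB/NVB the range is about +4% to −20% if participants meet two different students. Validity is at risk only if the roster was uneven over arm or encounter type, and only the actual counts can show that.

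These sizes rest on an assumed patient share of 0.30 and student share of 0–0.30, and on a linear model standing in for the GEE.

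**What to change.** 1. Add the student who played each encounter as a five-level fixed factor in the VECTORS and OPTION-5 models, or at minimum state this as a sensitivity analysis beside the planned model. A fixed factor is preferable to clustering on student, because five clusters are too few for a reliable robust variance.
2. Tabulate student by arm and student by encounter type, with scores by student. This shows whether the roster was even and gives the follow-on study a between-clinician variance. With five students that estimate is rough and should be presented as such.
3. Reword the Discussion claim, for example: clinician behaviour was standardised by script and training, and analyses were adjusted for student.

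Cost: four degrees of freedom, one table, one sentence, and a standard error for the arm difference up to about 5% wider if students hardly differ. The article reports the data as ready for analysis and planned audio-video recording of the encounters, so the student should be identifiable, although it does not say that a student identifier is kept.

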#### Simulation Scripts

We developed 2 simulation scripts (values-based and nonvalues-based), with guidance from a simulation expert and 3 clinical oncologists.

#### Values-Based Simulation Script

A review of literature was performed to assess the best practices in communication and SDM during clinical encounters [21,32-37]. The resulting VB script was designed to model a “high-quality” encounter in which clinicians focus on discussing and incorporating patients’ values into treatment decisions. The quality of the encounter was structured using three levels of situational awareness [38], modified for clinician and patient engagement.

**Level 1—Gathering Information:** Identifying what matters most to the patient when making a treatment decision.**Level 2—Processing Information:** Exploring how the patient’s values are impacted by treatment options.**Level 3—Projecting Information:** Anticipating what will occur after making a decision based on that information.

This script was developed to ensure the oncologist addressed all 3 levels during the encounter, supporting a values-aligned decision-making process.

#### Nonvalues-Based Simulation Script

The NVB simulation script was designed to model a “lower quality” encounter in which the oncologist focuses on treatment decisions without explicitly addressing the patient’s values. In these encounters, any shift toward values-based discussion must be initiated by the patient, referred to as “patient agency.”

For example, if a participant mentions caring for their grandkids and expresses concern about how treatment may affect that role, the clinician is prompted to transition to level 2 of the VB framework (processing information about how the patient’s values are impacted). This may also prompt the clinician to go to level 1 (gathering information about what the patient values most). After addressing the patient’s concern, the clinician returns to the NVB script to inquire if the patient is then ready to make a treatment decision. During NVB encounters, clinicians are instructed not to advance through the values-based levels unless explicitly prompted by the patient. This structure ensures that values-based engagement in NVB encounters occurs only in response to patient-initiated cues.

See Figure 2 for the simulation script schema. This schema was used to support both the development of simulation scripts and medical student training for conducting VB and NVB encounters.

**Figure 2 figure2:**
[figure not shown]
Simulation script schema.

#### Values Elicitation and Clarification of Treatment Options Rating Scale

We developed a novel rating scale called the Values Elicitation and Clarification of Treatment Options Rating Scale (VECTORS). VECTORS is a 7-item rating scale that includes 3 domains: rapport building (1 item), clinician engagement (3 items), and patient engagement (3 items). VECTORS uses a Likert-type scale with 3 response options representing a 10-point scale (0=no effort observed, 5=moderate effort was observed, and 10=exemplary effort was observed). Higher scores reflect higher quality of values-clarification processes.

Table 1 displays the rating score criteria for each of the 7 items in VECTORS. VECTORS was established following the same situational awareness framework and review of literature as described under the simulation script development to rate the quality of values-clarification processes that occurred during patient-clinician encounters.

**Table 1 table1:** Values Elicitation and Clarification of Treatment Options Rating Scale (VECTORS).

Rating score			Scoring criteria	Rating example
**Rapport building (clinicians and patients engaged in rapport building)**				
	0		Patients and clinicians did not engage in rapport building.	N/A^a^
	5		Patients and clinicians engaged in rapport building moderately well, but only surface-level discussion.	*Clinician*: “*How are you doing today?, How was your drive in?, etc.”**Patient*: “*I’m doing okay, it’s a nice day outside, and the drive in wasn’t too bad.”*
	10		Patients and clinicians engaged in rapport building extremely well. Patients and clinicians engage in a dialogue to learn more about one another.	*Clinician*: *“Tell me about yourself, what are some of things that you enjoy doing*.” *Patient*: “*I’m 62 years old, married and have 2 kids. I enjoy going for walks with my dog, playing the violin and going out to restaurants with my friends*.” *Clinician*: “*That sounds very enjoyable. I appreciate you sharing that with me. I hope to learn more about you as we go through this journey together. I’d like to tell you more about myself, and the role that I will have in your cancer care.”*
**Clinician engagement**				
	**Level 1: Gather information (clinicians discussed what their patients value most)**			
		0	Patients’ values not discussed, no reference or acknowledgment.	N/A
		5	Discussed moderately well. Clinician initiates discussion to understand how the patients’ values might inform a treatment decision but does not follow up with questions to learn more about what that means to the patient. Additional conversation does not ensue to understand how their values would be applied to making a treatment decision.	*Clinician**:** “I would like to talk about what you value most when thinking about treatment options as this can help us decide on the treatment pathway that is best for you. Patient: [responds]. Clinician: “Thank you for letting me know, that’s important for us to think about when making a treatment decision.”*
		10	Discussed extremely well. Clinician initiates a discussion to understand how their patients’ values might inform a treatment decision. Follows up with questions to learn more about what that means to the patient.	*Clinician:* “*I would like to talk about what you value most when thinking about treatment options as this can help us decide on the treatment pathway that is best for you. Would that be okay if we talked about that?” Patient: [responds]. Clinician: “Can you tell me what maintaining your day to day activities mean to you. What concerns do you have about this?”*
	**Level 2: Process information (clinicians discussed how treatment options may impact what patients value most)**			
		0	Not discussed, presented treatment options, but did not mention how the patients’ values may be impacted.	N/A
		5	Discussed moderately well.	Treatment options were presented, but the conversation only addressed how the clinician’s recommended option might affect what the patient values.
		10	Discussed extremely well.	Treatment options are presented, and the conversation addressed how each option might affect what the patient values.
	**Level 3: Project information (clinicians confirmed their patient understood how treatment options may impact what they value most)**			
		0	Not discussed, no reference or acknowledgment.	N/A
		5	Discussed moderately well. Clinician asks a simple question confirming understanding of the treatment the clinician recommended.	*Clinician:* “*Do you have questions about this treatment?”*
		10	Discussed extremely well. Clinician confirms the patient understood or helps clarify any misunderstandings.	*Clinician:* “How would you describe both treatment options to your family?”, or “In your own words, how will each treatment impact the values we previously discussed?” or “In your own words, what does choosing this treatment mean to you?”
